### 5.5. Data Collection and Validation

Data will be collected by trained personnel using standardized templates designed to capture all required information and ensure accurate patient identification. The Principal Investigator will supervise data cataloging and oversee adherence to data management procedures. The templates will be based on a methodological catalog that has been in continuous use at the hospital for approximately 20 years and is regularly updated to maintain accuracy and relevance. All metadata will be stored in a secure system for future use, verification, or publication, with access restricted to authorized personnel only.

The research dataset will comprise multiple data types—including narrative descriptions, numerical calculations, graphic files, and outputs from medical devices—and is expected to total no more than 0.5 TB. To ensure high data quality, the study will implement a comprehensive set of quality control procedures. These include real-time validation at the point of data entry (e.g., automated field checks), logical and consistency analyses, continuous monitoring and auditing to identify deviations from established standards, proactive management of missing data through timely detection and corrective measures, and statistical procedures to identify outliers and evaluate trends. Personnel responsible for data collection and entry will undergo dedicated training, and all procedures will be validated and pilot-tested on small samples prior to full-scale implementation. Collectively, these measures will ensure that the resulting dataset is accurate, reliable, and suitable for subsequent analyses and applications.

### 5.6. Statistical Methods

A detailed statistical analysis plan will be finalized before database lock and before the final between-group analyses. It will retain the protocol-defined populations, 9:1 randomization ratio, primary and secondary outcomes, sample-size assumptions, and significance threshold, while setting out the planned adjusted, supportive, sensitivity, and missing-data analyses in greater detail.

The oncology and non-oncology populations are predefined and will be analyzed separately. For each primary outcome, the principal analysis will estimate the effect of assignment to the RESET pathway compared with standard perioperative care during the protocol-defined follow-up period.

The three primary outcomes are separate primary outcomes rather than co-primary endpoints requiring simultaneous significance. Each outcome will be evaluated separately within each of the two predefined clinical populations, yielding six outcome-by-population primary hypothesis tests. No hierarchical or gatekeeping order and no composite primary endpoint are imposed. The multiplicity-controlled decision rule for confirmatory conclusions is specified below.

Primary randomized analyses will follow the intention-to-treat principle. All randomized participants will be analyzed in the group to which they were assigned, regardless of incomplete uptake of RESET, discontinuation or limited use of the mobile application or activity-monitoring wristband, missed prehabilitation consultations, or incomplete adherence to individual recommendations. These events will be recorded as measures of adherence and implementation but will not lead to reassignment or exclusion from the intention-to-treat analysis.

Per-protocol analyses will be performed as supportive analyses. The criteria for the per-protocol population will be defined prospectively in the statistical analysis plan before treatment effects are examined and will be based on major eligibility, randomization, or intervention-delivery deviations. Adherence will also be evaluated as a protocol-defined secondary and implementation outcome.

Each of the three binary primary outcomes—prolonged index hospitalization, unplanned hospital readmission within 30 days after discharge, and at least one postoperative complication within 30 days after surgery—will be analyzed using logistic regression. Numbers and proportions of events will be reported for each randomized group together with treatment-effect estimates and confidence intervals.

Adjusted analyses will use a parsimonious set of baseline factors with clear prognostic relevance—age, sex, study site, study year, ASA class, Charlson Comorbidity Index, and broad surgical-procedure category—subject to final prospective specification in the statistical analysis plan. Unadjusted randomized comparisons will also be reported. Measures of adherence or intervention exposure recorded after randomization will not be used to adjust the principal treatment-effect models.

Repeated outcomes will be analyzed primarily using mixed-effects models appropriate to the measurement scale. Continuous repeated outcomes will be assessed with linear mixed-effects models, and binary, ordinal, or count repeated outcomes with generalized linear mixed-effects models using an appropriate link function. Models will include randomized group, assessment time point, and the group-by-time interaction, with a participant-level random intercept to account for within-participant correlation. Baseline handling, the covariance structure, any random slopes, the treatment of study site, and any additional prespecified prognostic covariates will be defined in the SAP before treatment effects are examined. Repeated-measures ANCOVA will be restricted to supportive or sensitivity analyses.

Effect estimates will be reported with confidence intervals in addition to *p* values. The protocol-defined two-sided α = 0.01 threshold will be retained as the nominal design threshold, and principal primary-effect estimates will be accompanied by 99% confidence intervals. Consistent with the protocol, nominal *p* values between 0.01 and 0.05 may be described as exploratory. For the six primary hypotheses, however, confirmatory status will be determined by the multiplicity-adjusted decision rule below; any primary result that does not satisfy that rule will be considered non-confirmatory irrespective of its nominal *p* value.

The approved protocol specified α = 0.01 but did not define a formal family-wise multiplicity procedure. Because each of the three primary outcomes will be tested separately in each of the two predefined clinical populations, the confirmatory primary family comprises six outcome-by-population hypothesis tests. As a prospective safeguard specified before database lock and before examination of treatment effects, Holm’s step-down procedure will be applied across all six primary *p* values to control the family-wise error rate at α = 0.01 across both outcomes and clinical populations. A confirmatory positive finding for a specific outcome-population hypothesis will require an estimated effect in the prespecified direction favoring RESET and a Holm-adjusted two-sided *p* value < 0.01. Simultaneous significance of all three outcomes is not required. Rejection of one or more hypotheses under this procedure will support a confirmatory conclusion only for the corresponding endpoint(s) and clinical population(s); it will not imply benefit for the remaining primary outcomes or for the other population. All six primary results will be reported regardless of statistical significance.

The amount and reasons for missing data will be summarized by randomized group and clinical population. Primary outcomes will be obtained from the protocol-defined sources, including electronic health records, hospital information systems, and scheduled follow-up, subject to applicable consent and data-protection requirements. The approach to missing data will depend on their extent, pattern, and likely mechanism. Longitudinal models will use all available observations under their stated assumptions. Multiple imputation will be considered when appropriate, particularly when a missing-at-random assumption is clinically and statistically plausible and suitable auxiliary information is available. If missing primary-outcome data are substantial, sensitivity analyses will examine whether the conclusions remain robust under alternative assumptions. Complete-case analyses may be reported as supportive analyses but will not replace the intention-to-treat analysis.

Analyses performed while recruitment and follow-up are ongoing, whether for implementation monitoring or interim scientific reporting, will be descriptive or exploratory and will not be used for formal efficacy stopping decisions. The final protocol-defined primary analyses will be performed after completion of the planned follow-up and database lock.

Data management and preprocessing will be conducted using spreadsheet software and R (version 4.4.2 or higher) [43], with established R packages including the tidyverse ecosystem [44]; JASP or Jamovi may be used as complementary tools.

During revision in response to peer review, ChatGPT (OpenAI, GPT-5.6 Sol) was used to assist with language editing and drafting of revised methodological descriptions. It was not used to generate or analyze study data. All methodological and statistical decisions and the final wording were reviewed and approved by the authors, who take full responsibility for the manuscript.

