Exploratory comparisons with eligible non-participants will be kept separate from the randomized analyses. Because RESET includes clinically heterogeneous operations and specialty-specific risk profiles, a single propensity-score model would not be appropriate across all surgical populations. Where propensity-score methods are used, the model will be defined prospectively within clinically coherent groups before outcomes are compared. Adjustment will be limited to characteristics recorded before the decision to participate and available in a comparable form for both participants and non-participants. The covariate set will be selected from routinely available demographic, center, calendar-period, and procedural characteristics, with additional specialty- or procedure-specific baseline factors included when clinically relevant and consistently available. Variables arising after study participation will not be used. Covariate balance and overlap between groups will be checked before adjusted comparisons are interpreted. These analyses will remain exploratory and will not influence the primary randomized treatment-effect analyses. For transparency, the prespecified core covariate set for any propensity-score analysis will comprise age, sex, study site, calendar year, ASA physical status class, Charlson Comorbidity Index, and broad surgical-procedure category. Propensity-score analyses will be undertaken only within clinically coherent groups in which these core variables are recorded before the decision to participate and are available in a comparable form for participants and eligible non-participants. Any additional specialty- or procedure-specific baseline covariate must be clinically justified and defined before outcome comparison and must be consistently available in both groups.

Analyses of accumulated data may be conducted annually to support implementation monitoring and prespecified interim publications. Final analyses will be performed after completion of follow-up. Study year and site may be included as covariates to evaluate temporal and center-related variation; these analyses will not replace the prespecified randomized comparison.

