Because Holm’s procedure is step-down, α = 0.00167 is a conservative single-hypothesis benchmark rather than the threshold applied to every ordered test. The detectable effects in Table 2 should therefore be interpreted as worst-step design-sensitivity benchmarks; the full family-wise operating characteristics depend on the joint pattern of the six primary *p* values. The SAP, finalized before database lock and before treatment effects are examined, will document these assumptions and may supplement them with simulation-based scenarios using blinded pooled event-frequency information. This prospective characterization will not alter the recruitment target, allocation ratio, endpoints, or protocol-defined α and power targets.

The protocol did not provide a detailed narrative rationale for the α = 0.01 and 95% power combination, so the original specification is distinguished here from the explanatory rationale added in this revision. Retaining a stringent α reduces the risk that isolated primary findings are over-interpreted in a trial with multiple primary comparisons and an extensive secondary and implementation program, while the 95% power target reflects a preference for stronger assurance that clinically meaningful effects are not missed. With the fixed, large recruitment base, this conservatism translates into a larger minimum detectable effect rather than a larger recruitment target: for prolonged hospitalization in the oncology population, the detectable absolute reduction is approximately 4.6 percentage points under α = 0.05 with 80% power, 6.8 percentage points under α = 0.01 with 95% power, and 7.6 percentage points using the conservative first Holm step at α = 0.00167 with 95% power. The Investigators considered this evidential standard appropriate because RESET is intended to inform system-level implementation and potentially reimbursement, where false-positive conclusions would have substantial organizational and financial consequences.

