## 6. Discussion

RESET evaluates an integrated perioperative pathway combining individualized prehabilitation, coordinated inpatient care, structured discharge planning, and transitional care. Existing evidence suggests that prehabilitation can improve functional capacity and selected postoperative outcomes, but effects vary across populations, intervention content, and implementation settings [1,4,6,7,8,9,10,11,12,13,14,15,16]. The present trial therefore tests the effectiveness of the integrated pathway rather than assuming that benefits of individual elements will translate directly to the complete RESET model.

The clinical rationale is particularly relevant to patients with cancer and older surgical patients, in whom limited physiological reserve, frailty, multimorbidity, nutritional deficits, and short preoperative windows may modify response to optimization. Prolonged hospitalization and readmission are also multifactorial outcomes that reflect perioperative morbidity, discharge preparation, access to follow-up, patient and caregiver support, and organizational factors [29,30,31]. RESET addresses these domains within one coordinated pathway spanning the preoperative, inpatient, and 30-day post-discharge periods.

The 9:1 allocation increases experience with delivery and implementation of RESET while preserving a randomized standard-care comparator, but the smaller control group necessarily reduces statistical efficiency compared with balanced allocation. The protocol’s generic reference calculations should therefore not be interpreted as guaranteeing 95% power for every endpoint-population hypothesis. The current manuscript reports conservative endpoint-specific design-sensitivity benchmarks under the planned allocation and the first Holm step; the SAP will document the full family-wise operating characteristics before database lock and before treatment effects are examined.

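### The SAP deadline is worded inconsistently and is not tied to the annual analyses, so by-arm results could be seen or published while parts of the primary analysis are still open

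*Protocol article*

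**What the plan says.** The protocol article gives the SAP two different deadlines.

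- Section 5.6, opening sentence: "A detailed statistical analysis plan will be finalized before database lock and before the final between-group analyses".
- Section 5.4: "The SAP, finalized before database lock and before treatment effects are examined, will document these assumptions". Section 6 repeats the condition: "the SAP will document the full family-wise operating characteristics before database lock and before treatment effects are examined". Section 5.6 itself applies it to the per-protocol criteria, the mixed-model details and the Holm rule.

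On work done while the trial is running, section 5.3 states: "Analyses of accumulated data may be conducted annually to support implementation monitoring and prespecified interim publications". Section 5.6 adds that analyses made during recruitment and follow-up, "whether for implementation monitoring or interim scientific reporting, will be descriptive or exploratory and will not be used for formal efficacy stopping decisions". It then says: "The final protocol-defined primary analyses will be performed after completion of the planned follow-up and database lock".

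Section 7 gives 16 February 2026 as the start of recruitment and 16 May 2030 as the anticipated primary completion. Section 4.2.2 says that analysts are kept unaware of allocation only where feasible, and that the staff delivering RESET know the allocation.

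**The concern.** The word *final* in section 5.6 leaves room for between-group analyses before the SAP exists. Sections 5.3 and 5.6 create occasions for them, and nothing links SAP sign-off to the first such occasion. If an annual report shows outcomes by arm, the deadline in section 5.6 can still be met while the one in sections 5.4 and 6 has been broken.

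Two things are at stake. The first is the credibility of the confirmatory result, if choices that move the six primary p values are made with arm differences in view. The second is the conduct of the trial. Published arm differences could influence who consents, how control patients are cared for, when patients are discharged (which decides the 14-day endpoint), and how readily minor complications are recorded, since section 5.1 counts Clavien–Dindo grade I as an event. Signing the SAP early would deal with the first but not the second.

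**Working it through.** **1. The passages side by side.**

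| Place | SAP or analysis timing | Limited to non-comparative data? |
|---|---|---|
| 5.6, opening | Before lock and before the *final* between-group analyses | Not stated |
| 5.4 and 6 | Before lock and before treatment effects are examined | Yes in effect, if honoured |
| 5.3 | Annual analyses and interim publications | No |
| 5.6, near the end | Ongoing analyses descriptive or exploratory, no efficacy stopping | No |

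Section 5.4 specifies blinded pooled event frequencies where it means them. Sections 5.3 and 5.6 carry no such limit on the annual analyses.

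**2. What is fixed and what is open.** Already fixed are the three outcomes, the two populations, intention-to-treat, logistic regression, a list of seven covariates, and Holm over six tests at 0.01. Still open for the primary p values are:

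- the final covariate specification, which section 5.6 leaves to the SAP;
- the handling of missing primary outcomes, which section 5.6 makes dependent on extent, pattern and mechanism;
- the p value that enters Holm. Adjusted and unadjusted results are both to be reported. The wording leans towards the adjusted model but does not say so.

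**3. How much a look would reveal.** From 16 February 2026 to 16 May 2030 is 1550 days. The anniversaries fall at days 365, 730, 1096 and 1461. With uniform accrual up to primary completion (an assumption), the information fraction is t = day/1550, and an interim estimate correlates √t with the final one. Expected controls are 570t (oncology) and 320t (non-oncology).

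| Look | t | √t | Controls, oncology | Controls, non-oncology |
|---|---|---|---|---|
| Feb 2027 | 0.235 | 0.49 | 134 | 75 |
| Feb 2028 | 0.471 | 0.69 | 268 | 151 |
| Feb 2029 | 0.707 | 0.84 | 403 | 226 |
| Feb 2030 | 0.943 | 0.97 | 537 | 302 |

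The early looks are noisy; the last nearly gives the answer.

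**4. What a results-driven choice could cost.** Suppose the more favourable of two analyses, such as adjusted and unadjusted, were chosen for each hypothesis. The error is P(max(|Z1|, |Z2|) > z) under the null, with an assumed correlation between the two statistics of 0.95 to 0.80. By simulation:

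- nominal 0.01: 0.0135 to 0.0167;
- first Holm step, 0.01/6 = 0.00167: 0.0023 to 0.0029.

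If all six hypotheses are null, the family-wise error is then at most 6 × 0.00234 = 0.014 to 6 × 0.00293 = 0.018, against the planned 0.01. This is a ceiling for a choice between two analyses, because it assumes that the choice is made on the final data. A choice made on interim data would gain less.

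**5. The design figures are not in question.** Take Table 2, oncology, prolonged hospitalization: 20.0% against 12.4%, n = 570 and 5170, two-sided alpha 0.00167 (z = 3.144).

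- Pooled risk = (570 × 0.200 + 5170 × 0.124)/5740 = 0.1316.
- SE under the null = √(0.1316 × 0.8684 × (1/570 + 1/5170)) = 0.0149.
- SE under the alternative = √(0.2 × 0.8/570 + 0.124 × 0.876/5170) = 0.0174.
- Power = Φ((0.076 − 3.144 × 0.0149)/0.0174) = 0.953, against the stated 95%.

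The other five rows reproduce as well (0.948 to 0.952). The fix leaves these figures unchanged.

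**The case against.** Most of the primary analysis is already public, and the stricter condition appears several times. If it is honoured, no one examines treatment effects before the SAP is signed, and the SAP-timing problem does not arise. That stands: the defect is one looser sentence, and annual analyses that are not tied to the stricter condition. It would be wrong to say that the SAP need only precede database lock, or that the primary analysis as a whole is unfixed. Two further items do not belong on the open list. Section 5.2 already gives the definition of cases without complications, and the per-protocol criteria are supportive and already carry the stricter deadline.

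It is also fair that no sentence says outcomes will be reported by arm. The interim publications are called prespecified, and their content may be set out in the full protocol, which is not shown. What remains is that the article permits by-arm reporting and does not rule it out.

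A reader might go further and infer that four looks inflate the type I error of the trial. Four equally spaced looks at a true null give a 2.9% chance of at least one p < 0.01, and 12.7% of at least one p < 0.05, for each hypothesis. Over six independent hypotheses these become about 16% and 56%. With full correlation within each population they are about 6% and 24%. They are chances of a misleading interim signal, not error rates of the final test. Section 5.6 bars efficacy stopping, places the primary analyses after lock, and makes any result that fails Holm non-confirmatory.

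On masking, aggregate results do not reveal any one patient's arm, and section 4.2.2 claims only non-disclosure. The risk to conduct therefore comes from changed expectations and behaviour, not from unmasking individuals.

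**Conclusion.** The point holds as an inconsistency that should be settled before the first annual analysis, since disclosure cannot be undone. Section 5.6 does not match sections 5.4 and 6, and the annual analyses are tied to neither deadline. Up to four looks could precede primary completion, with estimates correlating about 0.49 to 0.97 with the final ones under uniform accrual. Three inputs to the primary p values would be open at that time. A choice between two analyses could raise the first Holm step from 0.00167 to at most about 0.003, under the assumed correlations. The looks spend no alpha. The effect of published arm differences on conduct cannot be quantified from the document. It matters here because providers are unblinded and only one randomized participant in ten is a control, so changes in control-arm care would bear on a small group.

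**What to change.** - **Section 5.6, opening sentence:** require the SAP before *any* between-group analysis of outcomes, in place of the *final* ones, so that it agrees with sections 5.4 and 6.
- **SAP sign-off:** sign and date the SAP before the first annual analysis. It should name the p value (adjusted or unadjusted) that enters Holm, the final covariate set, and the handling of missing primary outcomes.
- **Sections 5.3 and 5.6, ongoing analyses:** state that until database lock, annual reports and interim publications contain no outcomes by randomized arm. They cover recruitment, RESET delivery and adherence, and data quality. The one exception is confidential by-arm data for safety oversight.

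The cost is a wording change, earlier work on the SAP, and the postponement of comparative interim papers to the final analysis. Recruitment target, allocation, endpoints, alpha and power stay as they are.
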